## Abstract

**Background:**

Acupuncture is effective in functional constipation (FC) treatment, but the central mechanism has not been well investigated. This trial will combine functional magnetic resonance imaging (fMRI) and positron emission tomography-computed tomography (PET-CT) to investigate the potential central mechanism of acupuncture treatment for FC.

**Methods:**

This is a multimodal neuroimaging randomized controlled trial. In total, 140 FC patients will be randomly allocated into four groups: the verum acupuncture group; the sham acupuncture group; the PEG 4000 group; and the waiting-list group. This trial will include a two-week baseline period and a two-week treatment period. Patients will receive 10 sessions of acupuncture, sham acupuncture, PEG 4000, or no intervention during the treatment period. The stool diary, Cleveland Constipation Score (CCS), Patient Assessment of Constipation Symptom (PAC-SYM), and Patient Assessment of Constipation Quality of Life Questionnaire (PAC-QoL) will be used to assess the clinical efficacy of different interventions. The MRI and PET-CT scans will be performed to detect cerebral functional changes in 15 patients in each group at baseline and at the end of treatment/waiting. Multimodal imaging data will be associated with clinical data to investigate possible correlation between brain activity changes elicited by different interventions and symptoms improvement.

**Discussion:**

We hypothesize that acupuncture can treat FC through normalizing the pathological alteration of the cerebral activity. The results of this trial will allow us to re-testify the therapeutic effects of acupuncture treating for FC and to investigate the potential central mechanism of acupuncture treatment for FC from direct (cerebral glucose metabolism) and indirect (contrast of oxyhemoglobin and deoxyhemoglobin) approaches.

**Trial registration:**

Chinese Clinical Trial Registry, ChiCTR1800016658. Registered on 14 June 2018.

**Electronic supplementary material:**

The online version of this article (10.1186/s13063-019-3410-8) contains supplementary material, which is available to authorized users.

## Background

Functional constipation (FC) is a common functional gastrointestinal disease (FGID) which is characterized by persistently difficult and low frequent defecation, often accompanied with straining and incomplete sensation but without organic abnormality of the lower abdomen [1, 2]. As a worldwide public health issue, the prevalence of FC is in the range of 12–19% in North America [3] and is about 14% in Asia [4], 19.2% in Europe, and 19.7% in Oceania [5]. Although FC is not life-threatening, it seriously influences FC patients’ quality of life (QoL) and has high medical costs [6–8]. The general measures to manage FC contain lifestyle modification and medication. Lifestyle modification, such as dietary fiber intake and physical activity, are recommended to improve bowel movement, whereas the efficacy still remains uncertain and the strength of recommendation is weak [9, 10]. Medicines, which are conventionally prescribed to FC patients, such as osmotic laxatives, stimulant laxatives, gastrointestinal prokinetic agents, and spasmolytic, are reported with definite efficacy, but the side effects of the majority of medicines, such as electrolyte disturbances, dehydration, bowel cramps, and esophageal obstruction, cannot be neglected [10]. As a result, seeking an effective complementary and alternative therapy with few side effects for FC has drawn the attention of both physicians and patients.

Acupuncture, as a widely used complementary and alternative therapy originating from ancient China, has been used to manage constipation for thousands of years. In recent years, many high-quality randomized controlled trials (RCTs) have also demonstrated the efficacy of acupuncture treating for FC [11–15]. For example, Liu et al. found that electro-acupuncture could significantly increase the frequency of spontaneous defecation with rare adverse events in chronic severe constipation [12]. Our recent study also identified that manual acupuncture at Tianshu (ST25) and Shangjuxu (ST37) acupoints were as effective as Mosapride intake in improving spontaneous bowel movements (SBMs) in chronic FC [16]. With the clinical effects being successfully acknowledged, the mechanism of acupuncture treating for FC has also become a focus in acupuncture research [17, 18]. Several studies have found that acupuncture may treat FC by promoting the gastrointestinal motility [19], modulating peripheral gastrointestinal hormones [20], and keeping the balance of excitatory and inhibitory neurons in the enteric nervous system (ENS) [21]. However, the central integration [22, 23], an essential node of acupuncture treatment for FC, has rarely been explored. In previous studies, we found that the therapeutic effects of acupuncture for functional dyspepsia (FD) [24] and functional diarrhea [25] were closely related to regulating the cerebral activity of disease-related regions. Whether the effects of acupuncture on FC are correlated with modulating cerebral activity remains uncertain and is worthy of further investigation.

Therefore, we designed this multimodal neuroimaging trial, aiming to: (1) re-testify the therapeutic effects of acupuncture treating for FC by comparing verum acupuncture with sham acupuncture and Polyethylene glycol (PEG) 4000; (2) explore the potential central mechanism of acupuncture treatment for FC by combining functional magnetic resonance imaging (fMRI) and positron emission tomography-computed tomography (PET-CT); (3) and investigate the possible correlation of brain activity changes elicited by different interventions with symptom improvements.

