### Sample size

According to a previous systematic review [29] that compared the therapeutic effects of acupuncture, lactulose, and sham acupuncture for FC, the mean weekly improvement in SBMs of 2.46, 2.17, and 1.76 were found in the verum acupuncture, lactulose, and sham acupuncture group, respectively. We anticipate a mean weekly SBM improvement of 2.5 in the verum acupuncture group, 2.2 in the PEG 4000 group, 1.8 in the sham acupuncture group, and 0.9 in the waiting-list control group. Considering α = 0.05, 1-β = 0.8, and a standard deviation of 2.0, a sample size of 128 is needed, with a drop-out rate of 10%; a total of 140 FC patients will be finally recruited.

Based on previous neuroimaging studies [30, 31], 12–15 individuals in each group is the reasonable sample size for stable cerebral responses. Therefore, in this trial, 15 participants randomly selected from each group will be scanned by MRI and PET-CT.

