### Control

We choose conventional medicine (PEG 4000) as a positive control to evaluate the therapeutic effects of acupuncture and select the sham acupuncture as a control to re-identify the specific effects of acupoints. To preclude the interference of self-healing tendency of FC, a waiting-list group is also designed.

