### Data analysis

#### Clinical data analysis

The clinical data will be analyzed using SPSS 20.0 statistics software (IBM Co., Armonk, NY, USA) based on the per-protocol (PP) principle. Continuous variables on normal distribution will be described with means and standard deviation (SD). Continuous variables conforming to a skewed distribution will be described with median and inter-quartile range. Categorical variables will be described with percentages (%).

Clinical data from the four groups will be compared using one-way ANOVA; statistical analysis between two groups (group A and B, group A and C, group A and D) will be performed using Dunnett’s test. The comparison between baseline and end of treatment in each group will be carried out with a paired samples *t*-test. The clinical outcome stool diary and CCS scores will be compared at three timepoints using the repeated measures ANOVA. Clinical data on skewed distribution will be compared using a non-parametric test. Categorical variables will be compared using the *χ*^2^ test or Fisher’s exact test. The statistical significance threshold is set at 0.05 with the two-sided test.

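### An unqualified Dunnett test, read as single-step, is needlessly conservative for verum versus sham and versus PEG 4000; the step-down form gains a few points of power at the same family-wise error

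*Protocol article*

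**What the plan says.** The Background section gives the first aim as re-testing the effect of acupuncture by "comparing verum acupuncture with sham acupuncture and Polyethylene glycol (PEG) 4000". The waiting list is not named there. The Control section gives that arm a different role: "To preclude the interference of self-healing tendency of FC, a waiting-list group is also designed".

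Under Clinical data analysis, the plan is: "Clinical data from the four groups will be compared using one-way ANOVA". For the pairwise comparisons, "statistical analysis between two groups (group A and B, group A and C, group A and D) will be performed using Dunnett’s test", at a two-sided 0.05 threshold. No order of testing is given, and the text does not say whether the test is single-step or step-down.

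The Sample size section states the effects expected: "We anticipate a mean weekly SBM improvement of 2.5 in the verum acupuncture group, 2.2 in the PEG 4000 group", then "1.8 in the sham acupuncture group, and 0.9 in the waiting-list control group". With SD 2.0, α = 0.05 and 80% power it arrives at 128 evaluable patients and recruits 140.

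**The concern.** Single-step Dunnett compares every contrast in the family with one critical value, set for the case in which all three null hypotheses may be true. On the plan's means, the waiting-list contrast is by far the largest (1.6 SBM per week, against 0.7 for sham and 0.3 for PEG 4000), so it is the one most likely to be rejected first. Once it is rejected, holding the family-wise error at 5% needs only a two-contrast threshold for the two that remain. The single-step test goes on applying the three-contrast threshold.

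What is at stake is some power on exactly the two comparisons in the first aim. Their power is already low, and the loss buys no additional error control.

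**Working it through.** **Inputs.** All are from the Sample size and Study design sections: means 2.5 (A, verum), 1.8 (B, sham), 2.2 (C, PEG 4000) and 0.9 (D, waiting list); SD 2.0; 128 evaluable patients allocated 1:1:1:1, so 32 per arm; two-sided 0.05.

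**The plan's own figure.**
- The grand mean is (2.5 + 1.8 + 2.2 + 0.9)/4 = 1.85.
- Squared deviations are 0.4225, 0.0025, 0.1225 and 0.9025, summing to 1.45.
- Cohen's f = √(1.45/4)/2.0 = 0.6021/2.0 = 0.301.
- The four-group F test has power 79.9% at 31 per arm and 81.3% at 32 per arm.

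The stated 128 therefore reproduces as a size for the overall ANOVA. The waiting list alone supplies 0.9025/1.45 = 62% of the between-group variation.

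**Contrast scale.** The standard error of a difference is 2.0 × √(2/32) = 0.5. Noncentralities are 0.7/0.5 = 1.4 (A–B), 0.3/0.5 = 0.6 (A–C) and 1.6/0.5 = 3.2 (A–D).

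**Critical values** (128 − 4 = 124 df, shared verum arm, by simulation): 2.38 for three contrasts, 2.24 for two and 1.98 for one.

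**Hand check, single-step, normal approximation.**
- A–B: P(Z > 2.38 − 1.4) = P(Z > 0.98) ≈ 16%.
- A–C: P(Z > 2.38 − 0.6) = P(Z > 1.78) ≈ 4%.
- A–D: P(Z > 2.38 − 3.2) = P(Z > −0.82) ≈ 79%.

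**Simulated power**, 2 million trials with pooled error:

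| Contrast | Single-step | Step-down |
|---|---|---|
| A–B (sham) | 16.8% | 20.8% |
| A–C (PEG 4000) | 4.1% | 7.0% |
| A–D (waiting list) | 79.3% | 79.5% |

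Repeat runs differ by about 0.1 percentage point. With all 140 evaluable (35 per arm), verum versus sham has 18.5% single-step and 22.7% step-down.

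**Error control.** With all four means equal, both forms have a family-wise error of 5.0%. With the waiting-list effect real (1.6) and both other contrasts null, the chance of at least one false rejection is 3.6% single-step and 4.6% step-down. The single-step test leaves part of the 5% unused in just the situation the plan expects. No simulated trial had a contrast rejected by single-step and not by step-down. This follows from the construction: the first step uses the same critical value and later steps use smaller ones.

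**Dependence on the waiting-list mean.** Holding the other means fixed, step-down power for verum versus sham is 19.3% if the waiting-list mean is 1.5 and 18.2% if it is 1.8. The gain shrinks but does not reverse.

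**The case against.** Dunnett's test is a standard procedure for several comparisons with one common arm, it fits the family the protocol defines, and it controls the family-wise error. That stands: this is a choice that could be sharpened, not a mistake.

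The form is not stated, and a condensed article may leave it to a fuller plan. That also stands. Single-step is only the ordinary reading of an unqualified name. If step-down was intended, one word would settle it.

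A reader might infer that putting the waiting list in the family contradicts the first aim. The documents do not support that. The Control section presents PEG 4000, sham and the waiting list together as the chosen controls, and the Sample size section gives each an anticipated mean.

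A reader might also go further and propose a fixed order (waiting list, then sham, then PEG 4000), which gives verum versus sham about 28% on the plan's means. That figure is fragile:
- It needs sham before PEG 4000; with PEG 4000 first, sham power is 5.6%.
- It depends on the waiting-list mean of 0.9, the one anticipated mean without a counterpart in the review figures that the section quotes. At 1.5 the ordered power is 21.5%. At 1.8 it is about 14.6%, below the single-step test.

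The fixed order is therefore a trade-off and not an improvement that can be relied on.

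Finally, the stool diary is also assigned to a repeated-measures ANOVA. The power figures here concern only the one-way group comparison.

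**Conclusion.** The point holds as a modest matter of efficiency. Read as single-step, the planned test is valid but stricter than 5% family-wise control requires. Step-down Dunnett adds about 4 percentage points for verum versus sham (16.8% to 20.8%) and about 3 for verum versus PEG 4000 (4.1% to 7.0%), and costs nothing on the waiting-list contrast.

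This rests on the single-step reading, the plan's means and SD, equal arms of 32 and the one-way analysis. The size of the gain varies with the waiting-list mean, but its direction does not.

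It should not be read as the cause of, or the cure for, the low power on the first aim. Even with step-down, verum versus sham would be missed about 79% of the time on the plan's own figures (100 − 20.8). The sample size matches the overall four-group test and not either of those contrasts, and no choice of multiplicity procedure changes that.

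**What to change.** In Clinical data analysis, name the step-down form of Dunnett's test for the three verum contrasts, using the pooled ANOVA error. Order the contrasts by |t| and compare the largest with 2.38, the next with 2.24 and the last with 1.98, stopping at the first failure. These values are for 124 df and equal arms of 32; recompute them for the numbers actually analysed. Report ordinary Dunnett simultaneous intervals beside the tests.

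The cost is one sentence and a few lines of calculation. No patient, visit or treatment is affected. The Trial status section reports 26 patients included, so the change can be fixed in advance while the analysts remain blinded. The one drawback is that the intervals will not always match the step-down decisions: a contrast may be rejected while its interval still includes zero. The plan should say beforehand that the step-down test decides significance and the intervals describe the size of the effect.

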## Method and Design

### Study design

This is a multimodal neuroimaging RCT. A total of 140 eligible FC patients diagnosed with the Rome IV diagnostic criteria [26] will be recruited and randomized to four groups with a 1:1:1:1 ratio. Fifteen participants in each group will be randomly selected to undergo both MRI and PET-CT scans. Outcome assessments will be performed at three timepoints: baseline; mid-point; and the end of treatment/waiting (see Fig. 1 for a detailed study schedule).

**Fig. 1 Fig1:**
[figure not shown]
Study schedule: 140 eligible patients will be randomly allocated into four groups with a 1:1:1:1 ratio. Fifteen patients in each group will be randomly selected to undergo MRI and PET-CT scans. Imaging data and HRV will be collected at baseline and at the end of the two-week treatment/waiting . Clinical data will be acquired at three timepoints: baseline; mid-point; and the end of treatment/waiting. FC functional constipation, PEG polyethylene glycol, fMRI functional magnetic resonance imaging, PET-CT Positron emission tomography-computed tomography, HRV heart rate variability

This trial is reported in accordance with the Standard Protocol Items: Recommendations for Intervention Trials (SPIRIT) guidelines [27] (Fig. 2, Additional file 1) and follows the principles of the CONSORT and STRICTA [28].

**Fig. 2 Fig2:**
[figure not shown]
Standard Protocol Items: Recommendations for Interventional Trials (SPIRIT) schedule of the trial. This is a multimodal neuroimaging randomized controlled trial which includes a two-week baseline period and a two-week treatment period. In the baseline period, recruited patients will be screened according to the inclusion criteria and exclusion criteria; then, eligible FC patients will give informed consent and receive a physical examination. After allocation, the patients will receive 10 sessions of acupuncture, sham acupuncture, PEG 4000, or no intervention during the treatment period. The outcome assessments, MRI, and PET-CT scans are performed at baseline and at the end of treatment/waiting. In addition, the stool diary and CCS will also be evaluated at the mid-point (at the end of the first week of treatment/waiting). Physical examination (blood routine test and blood biochemical test) will be performed at the end of treatment to evaluate risks correlated with acupuncture and PEG4000. Adverse events will be recorded in the CRFs at any time during treatment. PEG polyethylene glycol, fMRI functional magnetic resonance imaging, PET-CT positron emission tomography-computed tomography, CCS Cleveland Constipation Score, PAC-SYM Patient Assessment of Constipation Symptom, PAC-QoL Patient Assessment of Constipation Quality of Life Questionnaire, SAS Self-rating Anxiety Scale, SDS Self-rating Depression Scale, HRV heart rate variability

### Participants

In the present trial, all potential FC patients matching the diagnostic criteria will undergo a physical examination including transabdominal ultrasound, dynamic electrocardiogram, routine blood test, routine urine test, routine stool test, and blood biochemical test (ALT, AST, BUN, Scr). Digestive physicians from the First Teaching Hospital of Chengdu University of Traditional Chinese Medicine (CDUTCM) will make the final diagnosis to include patients.

### Recruitment strategy

Participants will be recruited from the outpatient clinic in the digestive department of the First Teaching Hospital of CDUTCM and campus of CDUTCM from September 2018 to June 2020. The recruitment strategies include delivering leaflets at the outpatient clinic and campus, posting advertisements in billboards, and distributing news at the website of Acupuncture-Brain Research Center, CDUTCM (http://cdutcm.edu.cn/), and our WeChat public account.

### Diagnostic criteria

Rome IV Diagnostic Criteria for FC [26] which promulgated in 2016.

### Inclusion criteria

Patients fulfilling the following six items will be included: (1) matching the diagnostic criteria of FC according to Rome IV; (2) aged 20–40 years; (3) right-handed; (4) not having taken a gastrointestinal prokinetic agent or laxative at least 15 days before enrollment; (5) not participating in any other clinical trials in the past three months; and (6) having signed informed consent.

### Exclusion criteria

Patients matching any of the following five items will be excluded: (1) having any organic or metabolic diseases of the digestive, hematopoietic, endocrine, or immune systems or having any other severe primary diseases; (2) experiencing severe depressive or anxiety disorder; (3) having serious headache, migraine, or having a history of head trauma or gastrointestinal surgery; (4) women having severe dysmenorrhea, being in pregnancy or lactation, or intending to pregnant in the following six months; or (5) having contraindications of MRI or PET-CT scans such as claustrophobia, tattoo, or implanted ferromagnetic metal.

### Sample size

According to a previous systematic review [29] that compared the therapeutic effects of acupuncture, lactulose, and sham acupuncture for FC, the mean weekly improvement in SBMs of 2.46, 2.17, and 1.76 were found in the verum acupuncture, lactulose, and sham acupuncture group, respectively. We anticipate a mean weekly SBM improvement of 2.5 in the verum acupuncture group, 2.2 in the PEG 4000 group, 1.8 in the sham acupuncture group, and 0.9 in the waiting-list control group. Considering α = 0.05, 1-β = 0.8, and a standard deviation of 2.0, a sample size of 128 is needed, with a drop-out rate of 10%; a total of 140 FC patients will be finally recruited.

Based on previous neuroimaging studies [30, 31], 12–15 individuals in each group is the reasonable sample size for stable cerebral responses. Therefore, in this trial, 15 participants randomly selected from each group will be scanned by MRI and PET-CT.

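### The stated 80% power is that of the overall four-group F test and comes mainly from the waiting-list arm; verum versus sham has about 17% power and verum versus PEG about 4%

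*Protocol article*

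**What the plan says.** The Sample size section of the protocol article bases the trial on change in weekly spontaneous bowel movements (SBMs). The assumed means are: "We anticipate a mean weekly SBM improvement of 2.5 in the verum acupuncture group", followed by "2.2 in the PEG 4000 group, 1.8 in the sham acupuncture group, and 0.9 in the waiting-list control group". It continues: "Considering α = 0.05, 1-β = 0.8, and a standard deviation of 2.0, a sample size of 128 is needed". Recruitment is then set "with a drop-out rate of 10%; a total of 140 FC patients will be finally recruited". Patients are "randomized to four groups with a 1:1:1:1 ratio", so 128 is 32 per group and 140 is 35 per group. No test is named for the calculation, and no power is given for any pairwise comparison.

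The first of three aims at the end of the Background is to "re-testify the therapeutic effects of acupuncture treating for FC by comparing verum acupuncture with sham acupuncture" and with PEG 4000. The waiting list is not part of that aim. The Control section includes it to account for spontaneous recovery.

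Clinical data analysis plans a one-way ANOVA across the four groups. It adds that "statistical analysis between two groups (group A and B, group A and C, group A and D) will be performed" with Dunnett's test. "The statistical significance threshold is set at 0.05 with the two-sided test".

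**The concern.** A reader who takes the first aim and the sample size section together will assume that the 80% refers to verum against sham, or against PEG. The assumed differences are 0.7 and 0.3 SBM per week with an SD of 2.0, or 0.35 and 0.15 SD. With 32 per group, differences of that size cannot be detected with 80% power. The assumed difference from the waiting list is much larger, at 1.6 SBM per week (0.8 SD).

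This affects interpretation in two ways. A significant four-group F test would mainly reflect that waiting is worse than being treated, yet it could be reported as confirming an effect of acupuncture over sham. A non-significant contrast with sham or PEG is the likely result even if the trial's assumptions are exactly right, so it says little about whether the treatments differ.

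**Working it through.** **Inputs**, all from the protocol article: means 2.5 (verum, A), 1.8 (sham, B), 2.2 (PEG, C) and 0.9 (waiting list, D); SD 2.0; two-sided α = 0.05; target power 0.8; equal allocation; Dunnett's test for A–B, A–C and A–D.

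**1. Reproducing 128.**
- Grand mean = (2.5 + 2.2 + 1.8 + 0.9)/4 = 1.85.
- Squared deviations: A 0.65² = 0.4225; C 0.35² = 0.1225; B 0.05² = 0.0025; D 0.95² = 0.9025. Sum = 1.45.
- Cohen's f = √(1.45/4)/2.0 = 0.301.
- Noncentrality λ = n × 1.45/2.0². Power comes from the noncentral F distribution with 3 and 4n − 4 degrees of freedom.
- n = 31: λ = 11.24, power 79.9%. n = 32: λ = 11.60, power 81.3%.

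The smallest total reaching 80% is therefore 4 × 32 = 128, an exact match. The contrasts in the first aim do not give this figure. A two-sample calculation for 0.7 needs about 130 per arm (101 one-sided), and for 0.3 about 699 per arm.

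**2. What drives that power.** The waiting list contributes 0.9025/1.45 = 62% of the between-group sum of squares. For A, B and C alone the sum of squares is 0.247. At 32 per group λ = 32 × 0.247/4 = 1.97, and the three-group F test has 21.7% power.

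**3. Power of the planned contrasts at 32 per group.**
- Standard error of a difference = 2.0 × √(2/32) = 0.50.
- Degrees of freedom = 4 × 32 − 4 = 124.
- Two-sided critical values: 1.979 unadjusted; 2.377 for Dunnett with three comparisons (by simulation).
- Power comes from the noncentral t distribution with noncentrality = difference/0.50.

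| Contrast | Difference | Noncentrality | Power, unadjusted | Power, Dunnett |
|---|---|---|---|---|
| A–B, sham | 0.7 | 1.4 | 28% | 17% |
| A–C, PEG | 0.3 | 0.6 | 9% | 4% |
| A–D, waiting list | 1.6 | 3.2 | 89% | 79% |

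**4. Precision.** The 95% confidence interval half-width is 1.979 × 0.50 = 0.99 SBM per week, or 2.377 × 0.50 = 1.19 with Dunnett. Both exceed the 0.7 expected against sham.

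**5. Size needed for 80% on A–B.** About 130 per arm with an unadjusted test, or about 166 per arm with Dunnett. These are not interchangeable: 130 per arm gives only about 68% under Dunnett.

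**6. Sensitivity to the number analysed.** 140 × 0.9 = 126, slightly below 128; the overall F test then has about 80.6%. With all 140 analysed (35 per group), Dunnett power is 18.5% for A–B and about 4.4% for A–C.

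**The case against.** Several stronger readings are tempting, and the document does not support them.

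- *That 128 is miscalculated.* It is not. It reproduces exactly for the four-group ANOVA, which is the first comparison listed under Clinical data analysis. Powering on an overall test is legitimate. The fault is a mismatch between the powered test and the first aim.
- *That the protocol claims 80% for verum versus sham or PEG.* It makes no such claim; it prints one power without saying which test it belongs to. A reader may infer that it covers the first aim, and the text does nothing to prevent this.
- *That the 80% belongs to the F test and to nothing else.* Verum versus waiting list is also a planned contrast and has about 79% with Dunnett. But that contrast is outside the first aim, and its power comes from the same waiting-list mean.
- *That the trial sets out to declare acupuncture equivalent to PEG.* No equivalence or non-inferiority claim or margin is stated. The Background's remark about comparable efficacy concerns an earlier study with another drug. The caution about non-significant results is a safeguard, not a charge against the plan.

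It can also be said that the trial is mainly mechanistic, since two of its three aims concern brain imaging, and that an analysis plan not shown may say more. But clinical efficacy is listed first, and the 140 rests on SBMs alone (the imaging subset has its own justification). No further document can change the power that the printed means, SD and group size imply.

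**Conclusion.** The concern holds as a mismatch between power basis and aim, not as an arithmetic error. The 128 patients give about 81% power for the overall four-group F test (about 80.6% at 126), and most of that comes from the waiting list. For the two comparisons in the first aim, power under the planned Dunnett test is about 17% and 4%. If the trial's assumptions are exactly right, the sham contrast will miss significance about five times in six and the PEG contrast about 24 times in 25.

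The result rests on the protocol's means and SD, a common variance and 32 analysed per group. That the F test was the basis is an inference from the exact match, since the article does not name it. The conclusion depends on neither the multiplicity adjustment (28% and 9% without it) nor the dropout allowance.

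**What to change.** Reword the Sample size section, with no added patients:

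- State that the power of about 80–81% is that of the overall four-group one-way ANOVA F test, giving 81.3% at 128 analysed and about 80.6% at the 126 left after 10% dropout from 140.
- Print the contrast powers beside it, at 32 per group with Dunnett: verum versus sham about 17%, verum versus PEG about 4%, verum versus waiting list about 79%. Give the unadjusted values (28%, 9%, 89%) as well. If a required size for the sham contrast is quoted, label it: about 130 per arm unadjusted, about 166 with Dunnett.
- State that the sham and PEG contrasts are estimated with 95% confidence intervals, with an expected half-width of about 1.0 SBM per week (1.2 with Dunnett).
- State that a significant overall F test is not evidence of superiority over sham, and that a non-significant sham or PEG contrast is not evidence of equal effect.

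The cost is wording only. The downside is that the stated power looks less favourable for the first aim. The Trial status section reports 26 patients included, so the change can still be made while recruitment is at an early stage.
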